### Materials

Participants will supply their own smartphones and/or tablet devices. In total, 5 different apps will be used: (1) *Destressify* [30,31], (2) *MoodMission* [32-35], (3) *Smiling Mind* [36,37], (4) *MindShift* [15,38], and (5) *SuperBetter* [39,40].

All the apps are supported by published research demonstrating statistically significant efficacy for the treatment of anxiety and/or depression. Each app has an accompanying website with further information and an accessible privacy policy. Detailed information about each app and its accompanying research is provided in Multimedia Appendix 2.

### Measures

A number of measures of participants’ experiences and outcomes will be used, as described in the following sections.

#### Biographic and Demographic Features

The demographics questionnaire has been developed by the researchers to obtain information that will be examined to ascertain if any patterns in the outcome data are related to aspects of an individual’s demographic profile. Areas covered include mental health literacy [41], motivation to change [42], chronicity of anxiety and/or depression [43], and technology proficiency, all of which may influence results. Multimedia Appendix 3 contains the complete demographics questionnaire and all other measures used in this research.

#### Mental Health and Well-Being

A 3-phase model of psychotherapy outcomes [25] is applied.

Subjective well-being: SUDS ratings—participants rating their well-being in response to the question, “How do you feel today?,” with 0 indicating no distress and 10 indicating worst distress [44].Symptoms: the Depression Anxiety Stress Scale-21 short-form version (DASS-21) [45]. Participants rate their experience of symptoms of depression, anxiety, and stress over the previous week on a 4-point scale, ranging from 0 (did not apply to me at all) to 3 (applied to me very much or most of the time). Items in each subscale are summed to provide scores for symptoms of depression and anxiety, with higher scores indicating greater severity of symptomatology. The total scores for depression and anxiety subscales are multiplied by 2 to interpret the norms [46,47]. Severity ratings for the depression subscale are 0-9 (normal), 10-13 (mild), 14-20 (moderate), 21-27 (severe), and ≥28 (extremely severe). Norms for the anxiety subscale were set as 0-7 (normal), 8-9 (mild), 10-14 (moderate), 15-19 (severe), and 20+ (extremely severe). The DASS-21 has been shown to demonstrate sound psychometric properties and validity [48].Life functioning: the Outcome Questionnaire-45 second edition version (OQ-45.2) [49] is a 45-item self-report scale that measures overall interpersonal relationships and social role functioning in adults aged 18 years and older [50]. An index for overall life functioning is calculated [51]. Participants rate their feelings over the previous week on a 5-point scale, ranging from 0 (never) to 4 (always). The scale consists of both positive and negative items that are reverse-scored; higher scores indicate greater symptoms of distress and difficulties in interpersonal relations. A total score of ≥63 is indicative of clinically significant symptoms, with the subscale cutoffs for clinical significance being 35 for symptom distress, 14 for interpersonal relations, and 11 for social role [51]. The OQ-45.2 has demonstrated high internal consistency (α=.90) and test-retest reliability of *r*=.84 over a minimum 3-week period [52]. The OQ-45.2 has also shown good construct and concurrent validity in a community sample when using the total score as opposed to interpreting the 3 individual subscales [53].

#### Experience of App Usage

The Mobile Application Rating Scale-user version (uMARS) [54] is a 20-item questionnaire that records an individual’s rating on the quality of a mobile app. It contains multiple-choice and Likert-type responses and a free text field allowing users to provide a qualitative description of any aspect of the app or their experience of using the app that they wish to comment on. The uMARS contains 5 subscales: engagement, functionality, aesthetics, information quality, and a subjective quality appraisal. It has been found to have excellent internal consistency (α=.90) and good test-retest reliability [54].

### Procedure

Figures 1 and 2 illustrate the phases of this research. Recruitment commenced in January 2020.

**Figure 2 figure2:**
[figure not shown]
Flowchart of study and participant involvement.

#### Phase 1 (Prebaseline)

Web-based links to the information sheet for participants and consent form, the demographics questionnaire, and the mental health and well-being outcome measures (DASS-21 and OQ-45.2) are sent by email and SMS text messages and completed digitally by participants using the Qualtrics survey platform [55] and the OQ-Analyst platform [56]. Participants are screened for suitability to be in the proposed study by having their outcome measure and demographics questionnaire responses analyzed for evidence of severe anxiety and/or depression, suicidal ideation, or the presence of other severe mental illnesses such as psychosis. If researchers require further information from any participant, the participant will be contacted to clarify any queries or concerns. If a participant is deemed inappropriate for the proposed study, she/he will be directed by the researchers toward more appropriate forms of care.

#### Phase 2 (Baseline)

Accepted participants provide daily SUDS ratings for a minimum of 20 days or until a stable baseline profile of current psychological distress is achieved. At the end of this phase, the mental health and well-being outcome measures (DASS-21 and OQ-45.2) are completed.

#### Phase 3 (Intervention)

Participants are provided with generic instructions for all apps, links to both the Apple App Store and Google Play Store for their app, and specific instructions on how to use their app once it is downloaded (Multimedia Appendix 2). In addition, website links to information on the type of evidence-based framework their app uses and emergency contact information in the event of a mental health crisis are provided. Participants continue to supply daily SUDS ratings for the minimum 10-week intervention. Data analysis will be ongoing throughout this phase and will be used to assist in determining whether any participant’s mental health is significantly deteriorating. If a participant provides a SUDS rating of 10 for 2 consecutive days, they will be contacted for a check on their welfare. Similarly, if a participant’s SUDS ratings are above 8 for 5 consecutive days, they will also be contacted for a check on their welfare. We have chosen these cutoff values because the information provided to participants about the SUDS indicates that 8 is equal to their perception of feeling *very distressed* and 10 is equal to their perception of feeling the *worst distress.* The SUDS does not have a universal categorization label for each point on the scale, in addition to the number. Instead, it was designed to allow flexibility in an individual’s self-assessment [57] and labeling can vary from study to study. The mental health and well-being outcome measures (DASS-21 and OQ-45.2) and uMARS are completed at the end of this phase. If a participant’s responses on the outcome measures reveal a clinically significant decline in mental health compared with their responses at the beginning of the intervention, which places them in a severe category of mental illness, she/he will be contacted for a check on their welfare. In all cases, if a participant is categorized as being inappropriate for continuation in the proposed study, she/he will be directed toward more appropriate forms of care.

#### Phase 4 (Postintervention)

Participants provide SUDS ratings for at least 20 days following the completion of their official intervention period. Once a minimum of 20 SUDS ratings have been received, they will complete another DASS-21 and OQ-45.2. Participants are given information on all the apps so that they may explore the others if they wish.

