#### Phase 5 (Follow-Up)

Participants are followed up at 6 months, where they will be asked to complete the mental health and well-being outcome measures (DASS-21 and OQ-45.2).

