#### Clinical Significance and Statistical Reliability

Meaningful or clinically significant changes occur when an individual is in the dysfunctional (clinical) range at the commencement of treatment and in the functional (nonclinical) range at the end of treatment [61,62]. The clinical significance index (CSI) indicates whether individuals have made meaningful improvements to their emotional health and moved from being clinically dysfunctional to functional [63]. The reliable change index (RCI) verifies the statistical significance of any change in an individual’s score from pre- to postintervention [62]. This approach is particularly useful for single-case designs because it allows researchers to focus on individual functioning [64] and to adjust treatment if necessary. Jacobson and Truax [62] developed a classification system to describe the change in a participant’s mental health in a study’s conclusion: *recovered*=clinically significant and statistically reliable; *improved*=not clinically significant, but statistically reliable; *unchanged*=not clinically significant or statistically reliable; and *deteriorated*=clinically significant and/or statistically reliable in a worsening direction.

To determine the CSI, a cutoff point between the scores obtained by the functional and dysfunctional populations on a particular measure is identified [61,62]. Scores on either side of this point are statistically more likely to indicate whether an individual is functional or dysfunctional [61,62]. Normative data are required for both functional and dysfunctional populations for the measures being used. The CSI is based on the following formula [62]:

where 1 represents the nonclinical population and 2 represents the clinical population.

The RCI is a function of a measure’s standard deviation and reliability [61]. It measures an individual’s change in self-reported score from pretreatment to follow-up for statistical reliability. If an individual’s change exceeds 1.96 times the SE, the change is statistically reliable at *P*<.05 because it is unlikely to occur more than 5% of the time as a result of measure discrepancy or chance [61]. The RCI is calculated as follows [62]:

where S_diff_=√2(S_E_)^2^ and S_E_=*SD* of both groups×(√1−test-retest reliability).

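### The study gives everyone information on all five apps before the 6-month measures, so 6-month change cannot be cleanly credited to the randomised app in anyone who uses another

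*Protocol article*

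**What the plan says.** Under Recruitment, all 50 participants are randomised to an app, 10 per app. The Procedure section then sets this order:

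- **Phase 3 (Intervention):** 10 weeks on the assigned app. The DASS-21, OQ-45.2 and uMARS are completed at the end.
- **Phase 4 (Postintervention):** at least 20 days of SUDS ratings. "Once a minimum of 20 SUDS ratings have been received, they will complete another DASS-21 and OQ-45.2". The next sentence reads: "Participants are given information on all the apps so that they may explore the others if they wish". It is not tied to a date or to completion of the measures.
- **Phase 5 (Follow-Up):** "Participants are followed up at 6 months", with the DASS-21 and OQ-45.2 as the listed instruments.

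The section Clinical Significance and Statistical Reliability describes the RCI interval twice. First, the index "verifies the statistical significance of any change in an individual’s score from pre- to postintervention". Later, "It measures an individual’s change in self-reported score from pretreatment to follow-up for statistical reliability". The same section applies the Jacobson-Truax framework to the outcome measures across the phases, without excluding Phase 5.

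The removal criteria and the Data Exclusion section require only the pre- or baseline and postintervention measures. Neither mentions the 6-month measure.

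**The concern.** The study itself points every participant to the four apps they were not assigned, before its last outcome measurement. If someone improves between Phases 4 and 5 while using one of those apps, a 6-month classification reported by randomised app reflects both. Nothing described in the article would show which participants these are.

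The 6-month measure carries weight in this study. Previous Research lists missing long-term follow-up as a shortcoming of earlier work. Hypothesis 1 expects life functioning to improve last, so the latest OQ-45.2 is a natural place to look for that step. Research question 3 asks which app characteristics influence results, and any 6-month answer to it depends on knowing which app was used.

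The two RCI wordings add to this, because the article does not settle whether the 6-month score decides who is recovered, improved, unchanged or deteriorated.

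**Working it through.** **1. Timeline (Abstract, Study Design, Expected Time Frames).** Inputs: baseline 20 days = 2.9 weeks; intervention 10 weeks; postintervention 20 days = 2.9 weeks. All are minimum lengths. I take 6 months as 24 to 26 weeks.

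- Six months counted from the end of Phase 4: 2.9 + 10 + 2.9 + 24 = 39.7 weeks, or 41.7 with 26.
- Six months counted from the end of the intervention: 2.9 + 10 + 24 = 36.9 weeks, or 38.9 with 26.

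The article states approximately 40 weeks. Both countings are broadly compatible with that, and the first fits more closely.

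**2. How long the other apps are on offer before the 6-month measure.** The share is the window divided by the time from intervention start to follow-up.

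| Information given | 6 months counted from | Window (weeks) | Share |
|---|---|---|---|
| End of Phase 4 | End of Phase 4 | 24 to 26 | 24/36.9 = 65% to 26/38.9 = 67% |
| End of Phase 4 | End of intervention | 21.1 to 23.1 | 21.1/34 = 62% to 23.1/36 = 64% |
| Start of Phase 4 | End of Phase 4 | 26.9 to 28.9 | 26.9/36.9 = 73% to 28.9/38.9 = 74% |

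The assigned app has a prescribed period of 10 weeks. The window measures opportunity, not use.

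**3. Which results are exposed.**

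| Result | Information after Phase 4 measures | Information at start of Phase 4 |
|---|---|---|
| Baseline to end of intervention (Phase 3 measures) | Not exposed | Not exposed |
| SUDS, baseline against intervention | Not exposed | Not exposed |
| Postintervention SUDS (20 days) | Not exposed | Exposed |
| Baseline to end of Phase 4 measures | Not exposed | Exposed |
| Pretreatment to 6 months | Exposed | Exposed |

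The last row is exposed under either timing. The two rows above it depend on a timing that the article does not state.

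**4. Cases per app.** Study Design allows for 50% to 60% attrition: 10 × (1 − 0.5) = 5 and 10 × (1 − 0.6) = 4. The article says approximately 3 to 5. One affected case is 1/5 = 20% to 1/3 = 33% of an app's cases.

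**5. Rate of other-app use.** None is given, so the amount of mixing cannot be computed. As illustration only, assume that 10% to 30% of completers use another app, independently of each other. The chance of at least one such person is 1 − 0.9³ = 27% to 1 − 0.7³ = 66% among 3 completers, and 1 − 0.9⁵ = 41% to 1 − 0.7⁵ = 83% among 5. The documents offer no basis for that rate, and any trial of another app counts here, however brief.

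**The case against.** A reader might infer that the RCI is defined on the 6-month follow-up, so that the study's main classification is compromised. The article does not support that. Its first description of the RCI is "score from pre- to postintervention", and both data-requirement rules rest on pre- and postintervention measures. The wording "change in self-reported score from pretreatment to follow-up for statistical reliability" occurs in a general account of the index and may not mean Phase 5. What is left is one interval worded two ways.

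A reader might also infer that the 20-day postintervention window is contaminated. The sentence order in Phase 4 (ratings, then questionnaires, then app information) points the other way, though it is not an explicit rule. Nor does the article promise a per-app durability result at 6 months: it assigns stability of the effect to the postintervention period. Question 3 is not the tested hypothesis, and the uMARS ratings that inform it are collected at the end of Phase 3.

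Three further objections have force:

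- Use of the other apps is optional, so attribution fails only for those who use them.
- The apps are free and public, so holding back the list would not stop their use. By 6 months everyone has been treated, so the staggered baselines no longer provide a control in any case.
- The 3 to 5 cases are justified in the article for the SUDS time series, not for the 6-month questionnaires. The share per case is therefore a guide to how few people each app's result rests on.

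The complete forms are in Multimedia Appendix 3, which is not shown, so an item on other-app use may exist there. None of this removes the core point: the study prompts use of the other apps before its last measurement, and the article describes no means of identifying who acted on the prompt.

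**Conclusion.** The point holds in limited form. For participants who take up the Phase 4 offer, 6-month DASS-21 and OQ-45.2 change cannot be cleanly attributed to the randomised app. The other apps are on offer for about 21 to 26 weeks before that measure if the information comes at the end of Phase 4, and about 3 weeks longer if it comes at the start. This assumes minimum phase lengths and 24 to 26 weeks for 6 months.

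The documents do not allow the effect on any result to be quantified. With about 3 to 5 cases per app, a single affected case is a large share. The contrast from baseline to end of intervention stands under either timing. The one using the Phase 4 measures stands if the information follows them. The 6-month score decides the Jacobson-Truax class only if the second RCI wording is adopted and read as Phase 5. This is an inexpensive improvement to make, not a flaw that undermines the main analysis.

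**What to change.** 1. Send the information on the other apps after the 6-month questionnaires are returned. At minimum, state that it is sent only after the Phase 4 DASS-21 and OQ-45.2 are complete.
2. Add one item at the Phase 4 and Phase 5 questionnaires asking which apps were used since the intervention ended, unless the appendix forms already contain it.
3. State a single RCI/CSI interval as the app-attributable contrast: end of baseline to either end of intervention or postintervention, naming the measurement occasion. Bring the two RCI sentences into line with it.
4. Report 6-month results as secondary and descriptive, split by use of other apps.

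The cost is moving one message, one questionnaire item and a few sentences of analysis text. Participants would receive a list of already free, public apps later than planned. Use of other apps would be reduced and recorded, but not prevented.

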#### Phase 5 (Follow-Up)

Participants are followed up at 6 months, where they will be asked to complete the mental health and well-being outcome measures (DASS-21 and OQ-45.2).

#### Expected Time Frames

The daily SUDS text messages will take a few seconds to reply to; app use will be a minimum of 10 min per day, 5 days per week for 10 weeks; the mental health and well-being outcome measures (DASS-21 and OQ-45.2) are expected to take less than 10 min each to complete on 5 different occasions; and the demographics questionnaire completed in phase 1 and the uMARS questionnaire completed in phase 3 are expected to take 15 min each.

The proposed study will run for approximately 40 weeks. Data analysis will be completed by approximately December 2020. A write-up for publication is expected to be completed by January 2021.

### Data Analysis

#### Descriptive Statistics and Qualitative Accounts

Descriptive statistics will be used to compare individuals and augment other analytical techniques. The data obtained from the uMARS will be used to assist in gaining an enhanced understanding of participant attitudes toward their app. Depending on the amount of qualitative information provided by participants, it will be converted via a *content analysis* [58] and will be coded into networks that hierarchically classify, identify, and summarize key themes. Data obtained from the uMARS will be plotted, as explained in the Visual Inspection subsection.

#### Time Series Analysis

A process for conducting time series analyses for psychological research was described by Borckardt et al [59] using the *R* statistical software package. In the proposed study, the commencement of the intervention will be the predictor in a regression model that uses data before and after this point to determine if there has been a statistically significant impact on subjective distress, as measured by SUDS ratings. A minimum of 20 data points are required in each phase [20,26]. The *R* statistical package will use conventions of autoregressive integrative moving average (ARIMA) modeling to account for autocorrelated data [60] when building the model.

The time series analyses [59] will evaluate statistically significant changes across the phases of the proposed study. Overall level and trends across time will be considered, and if necessary, adjustments will be made for irregular variation effects. An *irregular factor* is similar to the error terms used in many statistical models, such as generalized linear modeling. The methods of making such adjustments differ depending on the nature of the collected data but may include the augmented Dickey-Fuller test, Durbin-Watson test and/or the Ljung-Box test as part of an ARIMA model.

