## Methods

### Study Design

This study is registered with the Australian and New Zealand Clinical Trials Registry (ANZCTR), which is a primary registry in the World Health Organization Registry Network (registration number: ACTRN12619001302145p).

A multiple baseline across-individuals design will be employed. Multiple baseline designs in mental health intervention studies are those where a baseline period of stability of symptoms is established before the intervention is introduced. In this way, each participant acts as their own control, and internal validity is demonstrated when there is no change in symptoms until after the treatment is introduced [18]. In the design to be used in this study, all participants commence the baseline period at the same time but start the treatment at different times after a minimum number of daily data readings (at least 20) have been received. This sequential commencement approach further strengthens the internal validity by reducing the likelihood of history, maturation, or other extraneous factors explaining any observed emotional or behavioral change that occurs simultaneously with the introduction of the treatment. The multiple data recordings allow for the use of analytical techniques such as a time series analysis [20,26] and will involve participants reporting ratings of subjective units of distress (SUDS) via SMS text messaging using a 10-point scale. In this design, 4 or more baselines are recommended [18,20], and these will follow the pattern shown in Figure 1.

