All 50 participants (10 for each app) will be randomized to an app and their position in the single-case design (ie, P1 to P10) using the web-based random number generator, *Research Randomizer* [29]. The full inclusion and exclusion criteria are presented in Textboxes 1 and 2, respectively. A financial reimbursement will be offered to participants of Aus $0.50 (US $0.33) per daily SUDS rating sent via a text message. The researchers acknowledge that financial payments have the potential to interfere with ecological validity, because a person in the community would not normally be paid for using a mental health app, and intrinsic motivation, because people could potentially use the app for the benefit of financial remuneration rather than for the value of improving their mental health. However, the low amount of remuneration being offered of approximately Aus $45.00 (US $29.41) on average is not considered payment for participation in the proposed study but rather reimbursement of personal expenses incurred while taking part in the proposed study. Given that the effectiveness of mental health apps has the potential to benefit those from low socioeconomic groups, being reimbursed for providing in excess of 80 text messages will alleviate reasons that a potential participant of lower socioeconomic background could provide for being out of pocket for the cost of sending text messages from their mobile phone. Therefore, it is envisaged that prospective participants will more likely have motivation to improve their mental health beyond receiving financial remuneration. In addition, this financial incentive will not be advertised, and participants will only learn about this when they provide consent when completing the demographics questionnaire.

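### The SUDS test is a within-person before/after regression that does not use the randomised staggered starts, so an event shared by participants can be counted as an app effect

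*Protocol article*

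**What the plan says.** The Study Design section of the protocol article describes a concurrent multiple baseline design: "all participants commence the baseline period at the same time but start the treatment at different times". It gives the purpose of the stagger: "This sequential commencement approach further strengthens the internal validity by reducing the likelihood of history, maturation, or other extraneous factors". Under Recruitment, all 50 participants (10 per app) "will be randomized to an app and their position in the single-case design", that is, P1 to P10.

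The Time Series Analysis section then sets out the SUDS test: "the commencement of the intervention will be the predictor in a regression model that uses data before and after this point". The adjustment named is "autoregressive integrative moving average (ARIMA) modeling to account for autocorrelated data". On other model terms it says "Overall level and trends across time will be considered", with adjustment for irregular variation if needed.

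Visual Inspection plans plots of up to 112 SUDS ratings and describes the reading of them as a personal judgement. The Abstract and Phase 2 (Baseline) make the start of treatment depend also on a stable baseline.

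**The concern.** A multiple baseline design guards against history because, on any calendar day between the first and last start, some participants have the intervention and others do not. An external event moves both groups; an app effect moves only those who have started. To draw on this, an analysis must compare participants on the same date.

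The stated test does not. It contrasts each series with its own earlier part ("each participant acts as their own control" in Study Design) and would give the same answer whatever the other participants' start dates. An event after the start shifts the contrast exactly as an app effect would.

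Replication does not repair this. The article treats consistent benefit in about 3 to 5 cases as robust, but a shared event produces false positives in several participants at once. The design also pays for its concurrent start: no late entrants and no replacement of dropouts, with 50% to 60% attrition expected.

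**Working it through.** **1. The plan's own figures.** 5 × 10 = 50 participants. With 50% to 60% attrition, 10 × 0.5 = 5 and 10 × 0.4 = 4 completers per app, against a stated 3 to 5 or so. The 112 ratings equal 16 weeks × 7 = 112. The phase minima give 20 + 70 + 20 = 110. The article gives no SD, autocorrelation, effect size or stagger length for SUDS (Figure 1 is not shown), so those below are assumptions.

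**2. Size of the shift.** Take a participant with 20 baseline and 70 intervention days, no app effect, and a lasting shared fall of size *d* that begins *k* days after the start. The difference in phase means is −*d* × (70 − *k*)/70:
- *k* = 5: 65/70 = 0.93 *d*
- *k* = 15: 55/70 = 0.79 *d*
- *k* = 35: 35/70 = 0.50 *d*

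Simulated autoregressive fits (starts spread over 2 days, event on day 25, 35 or 55) gave mean false effects of −0.90, −0.76 and −0.48 SD for a 1 SD fall, close to these fractions.

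**3. How often it is significant.** Assumptions: 10 participants, AR(1) 0.3, SD 1, no app effect, 200 runs per cell, two-sided 0.05, significant improvements counted (nominal 2.5%).

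| Scenario, 1 SD shared fall | Early event | Middle | Late |
|---|---|---|---|
| 2-day spread (day 25 / 35 / 55), step only | 76% | 54% | 21% |
| 2-day spread, at least 3 of 10 significant | 100% | 99% | 36% |
| 3-day steps (day 33 / 52 / 72), step only | 79% | 60% | 30% |
| 3-day steps, linear trend added | 23% | 6% | 0.3% |

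With no event the step-only rate was 3% to 4%. With a 0.5 SD event it was 6% to 32% over all staggers and timings. A joint level-and-slope test rejected in 9% to 28%, but it already rejected in 9% with no event, so only part of that is due to the event.

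**4. A test that uses the stagger.** Remove participant and calendar-day means, estimate a started/not-started term, and permute the start positions.
- Level under a shared fall and no app effect: 2% to 8% with 10 participants (one-sided nominal 5%, simulation error about ±3 points). With 25 completers and permutation within app: about 5% to 8%.
- Power, 10 participants, immediate effect of 0.5 SD / 1 SD: 27% / 63% (2-day spread), 43% / 93% (1-day steps), 76% / 99% (3-day steps), 91% / 100% (7-day steps).
- Power, 25 completers, AR(1) 0.4, SD 1.5, within-app permutation: 58% for an immediate 1-point step at a 2-day spread, but only 5% to 9% for a 1-point improvement that builds over 70 days. Day effects absorb slow change.
- Smallest attainable p within one app: 1/3! = 0.167, 1/4! = 0.042, 1/5! = 0.008 for 3, 4 and 5 completers. Pooled over five apps with 3 each: (1/6)⁵ = 0.00013.

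**5. Room for a stagger.** If 112 is the longest series, 112 − 110 leaves about 2 days. Ten positions at 1-day steps would need 20 + 9 + 70 + 20 = 119 ratings, and at 3-day steps 20 + 27 + 70 + 20 = 137.

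**The case against.** The strongest reply is that this is ordinary multiple-baseline practice. The protection belongs to the design, and the reader obtains it from staggered plots and replication at different dates, not from one p-value. Exact model terms may also sit in an analysis plan that is not shown. Part of this stands: the plots can use the stagger informally, and a fitted trend would remove much of the false signal. But the article does state the predictor and the data of the SUDS test, it does not commit to a trend term, and replication fails when the cause is common to all.

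A reader might infer more than the documents support:
- **That a shared event is counted as an app effect in every participant.** It can be. Significance depends on event size, timing and model terms, and with long staggers a late event misses the earliest starters.
- **That control of history is presented as the study's main strength.** Study Design says the stagger further strengthens validity; the strengths listed under Limitations and Strengths do not mention history.
- **That research question 1 is left without an answer.** It concerns clinically significant symptom change and rests mainly on DASS-21 and OQ-45.2. SUDS bears on the subjective-distress part of hypothesis 1.
- **That a joint model should replace the ARIMA models.** Hypothesis 1 expects progressive reductions in distress, the shape that the joint test detects worst.

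**Conclusion.** The point holds as a mismatch between design and test. The randomised, concurrent stagger does not enter the stated SUDS regression, so a significant result does not by itself exclude a shared event.

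The size is conditional. A lasting shared fall of 1 SD gave 21% to 79% false improvements per participant in the step-only scenarios tabulated, and 0.3% to 23% with a linear trend at 3-day steps. These figures rest on assumed autocorrelation, SD, event size and stagger. The shift in the before/after contrast follows from the arithmetic in step 2 and does not depend on the simulation.

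The change should be made, as an addition to the planned analysis. If 112 ratings is the longest series, the stagger is about 2 days, and any analysis that relies on it will be weak.

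**What to change.** 1. Keep the individual ARIMA models, name their level and trend terms, and state that on their own they do not rule out shared events.
2. Add a prespecified companion analysis over all participants with participant effects, calendar-day effects and a started/not-started term. Take the p-value from permuting start positions within app, pooled over apps. Report by-app results descriptively, since 3 completers cannot go below p = 0.167.
3. Base any statement that history is ruled out on this companion analysis.
4. Reconcile the stability-dependent start (Abstract; Phase 2) with the randomised position (Recruitment). The permutation is valid only if the start days follow from the randomised positions. State the stagger length and reconcile it with the 112 ratings.
5. State the assumption that dropout is unrelated to position, because the permutation would be applied to completers.

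**Cost.** Items 1 to 3 and 5 need wording and code, with no new participants or measurements. Item 4 may affect how starts are scheduled. The companion test detects abrupt change after the start and has little power for slow build-up or a very short stagger. A null result must not be read as no app effect.
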